### **Trial monitoring**

A clinical trials monitor independent from the investigator team monitored the trial. The monitor conducted an initiation visit to the site before the trial started to verify and document that all study staff were adequately informed about the study and that the IMP to be used had been received and stored accordingly on site.

During the course of the trial, interim monitoring visits took place at the health centre, the IMP storage facility, the site office and the laboratories.

During the visits, the monitor carried out a quality control of trial progress in respect to protocol and operating guidelines, data collection, completion of consent

forms, completion of study documents, SAE reporting, and samples and IMP management. Source data verification was conducted for all ICFs, eligibility criteria and SAEs.

The monitor inspected up to 10 % of participants CRFs for accuracy, completeness and consistency with source documents before data entry and reviewed the investigator's file.

At the end of each monitoring visit, the monitor discussed the findings with the study team and outlined what further actions should be taken.

The Monitor will conduct a close-out visit after all data queries have been resolved and the data base has been locked to ensure that all essential documents are completed and filed accordingly and are ready for archiving, that all IMPs have been accounted for and are returned to supplier or destroyed accordingly, and that all unused study materials are returned to suppliers or destroyed, as applicable.

The study team established, in addition, internal monitoring procedures to ensure review of all CRFs by study team members before any data was entered into the database.

### **Sample size rationale**

The original sample size (415 mother/baby pairs per arm) assumed a 15 % loss to follow-up (i.e. 353 participants in each arm for whom the primary endpoint is recorded). Based on data from a previous study [32], bacterial carriage (*S.aureus*, GBS or *S.pneumoniae*) on day 6 was assumed to be 60 % in the control arm. According to these assumptions, the study has 98 % power to detect a 25 % reduction in bacterial carriage (GBS, *S.pneumoniae* or *S.aureus*) and 88 % power to detect a 20 % reduction.

### **Statistical analysis**

A flow chart will be used to describe the number of mothers who were eligible, randomised and treated, and the number of samples obtained from mothers and children at each time point.

The adequacy of the randomisation procedure will be checked by comparing baseline characteristics of mothers (ethnicity, age, season enrolled, hours from treatment to delivery, mode of delivery, time to rupture of membrane, apgar score, multiple pregnancy) and newborns (sex, birth weight, gestational age) between arms. Some of these variables are measured post intervention, but are unlikely to be influenced by the intervention (time from treatment to delivery, mode of delivery, time to rupture of membrane, Apgar score). Prevalence of bacterial carriage in the mother pre-intervention will also be used to check comparability of baseline characteristics (NPS and vaginal swab).

The primary analysis will be based on intention to treat (ITT). We will include data on twins but will not adjust for the effect of clustering (the average cluster size will be close to 1 so the design effect will be negligible). A per protocol analysis will be conducted excluding samples from mothers who vomited less than 15 min after medication was taken, samples collected after the use of antibiotics, and samples arriving at the lab more than 8 h after collection.

The prevalence of bacterial carriage will be compared between arms at each time point (in NPS, vaginal swabs and breast milk). The prevalence of carriage will be presented separately for each species and combined (i.e., carriage of *S.aureus*, GBS or *S.pneumoniae*). In addition, carriage acquisition rates will be compared between arms for the periods 0–6 days and 7–28 days (acquisition will happen when a non-carrier will become carrier in the subsequent sample). Ratios of prevalence and 95 % confidence intervals will be calculated for each of these comparisons, and Fisher's exact test will be used to compute p-values for the comparisons of prevalence.

A Poisson regression model will be used to assess the effect of the intervention on prevalence of carriage across all time points. The model will include time, baseline carriage status of the mother, mother's age, ethnicity, season, sex of the newborn, and gestational age. Robust standard errors will be used to account for the dependence between observations from the same individual as well as the model misspecification (carriage status is binary and therefore does not follow a Poisson distribution).

To calculate prevalence of carriage at day 3 and day 6 we will use data from samples (NPS newborns and mothers, breast milk) collected within 1 day of the scheduled visit. At 14 days we will use samples collected between 12 and 18 days, and at 28 days we will use samples collected between 25 and 31 days. For vaginal bacterial carriage at day 8–10 we will use samples collected between 7 and 13 days. Samples were not collected after children received antibiotics. Where a sample was collected in lieu of the missing sample (i.e., before antibiotics were given) this will be used in place of the missing sample, even if it was collected outside the appropriate window period.

We will present analyses based on the available data. For the primary outcome we will conduct two additional analyses using the ITT cohort. First, a subgroup analysis in women who gave birth 2 h or more after taking the drug. And second, a sensitivity analysis using multiple imputation of missing data. In the imputation model, bacterial carriage in missing samples will be imputed from data on bacterial carriage at other time points and baseline demographic data (age and ethnicity for mothers, and sex and birth weight for newborns).

Changes in prevalence of bacterial carriage over time will be plotted for NPS in mothers and newborns, and breast milk. The plots will include point-wise 95 % confidence intervals for each prevalence estimate.

The numbers and rates of adverse events, serious adverse events (overall and specifically with a diagnosis of neonatal sepsis), purulent conjunctivitis, Chlamydial conjunctivitis, and deaths in newborns will be reported by trial arm. Rates of adverse events and serious adverse events will be reported in mothers. Rates will be compared between trial arms using Poisson regression, and robust standard errors will be used to allow for heterogeneity in the rates between individuals.

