### Blinding and Un-blinding

The packaging and labelling of the interventional medical product (IMP) was conducted by IDIFARMA. AZI and placebo were provided as tablets packed in blisters.

The randomisation list was created by an independent statistician/data manager and IDIFARMA numbered the blisters according to the list. One blister pack of IMP contained four tablets of 0.5 g of AZI or placebo (2 g in total). The active drug and the placebo looked identical and were not identifiable.

Sealed envelopes containing the individual treatment allocation were kept at the study site for emergency cases. The code could be broken for individual participants in cases of AE for which the investigational product needed to be known. The code was kept for the entire study period by the independent statistician of the Data Safety Monitoring Board (DSMB) and will be broken only after the database lock.

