### Randomization

IMP were labelled from 001 to 830. A random control digit was added to the identification number after a backslash – e.g. 001/1, to help detect transcription errors. The IMPs were assigned consecutively and in ascending order. The time when the drug was taken was recorded. The randomization number on the specific blister was written in the spaces (– – – / –) provided on the particular page of the case report form (CRF). Any vomiting (if it occurred), was documented including the timing and whether an IMP tablet was seen in the vomitus.

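### The per-protocol set keeps women in whom a study tablet was seen in the vomitus at 15 minutes or later, although the trial records that observation

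*Protocol*

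**What the plan says.** The Statistical analysis section of the Protocol makes intention to treat the primary analysis and adds a per-protocol analysis with three exclusions. The first is "excluding samples from mothers who vomited less than 15 min after medication was taken". The other two are "samples collected after the use of antibiotics, and samples arriving at the lab more than 8 h after collection"; they concern when a sample was taken and how it was transported, not whether the mother received the dose. No other section adds a dosing criterion for this set.

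The Randomization section describes what was recorded at dosing. On intake: "The time when the drug was taken was recorded". On vomiting: "Any vomiting (if it occurred), was documented including the timing and whether an IMP tablet was seen in the vomitus". The Blinding and Un-blinding section sets the full dose at four tablets of 0.5 g, 2 g in total.

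**The concern.** A per-protocol analysis is meant to show the effect among women who received the treatment as planned. A tablet seen in the vomitus is direct evidence that part of the dose was lost; elapsed time is only a proxy for that. The trial collects both, and the rule uses only the proxy.

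The set can therefore keep the clearer case of lost dose and drop the less clear one. A woman who vomits at 10 min with no tablet seen is removed. A woman who vomits at 20 min with a tablet seen is retained as fully dosed. The Protocol gives no reason for setting the tablet observation aside.

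At stake is the secondary estimate. Azithromycin-arm women who lost drug pull it towards no effect. Placebo-arm women who lost placebo tablets do not offset this, because they had no active drug to lose.

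**Working it through.** **Inputs.** From the Sample size rationale: 353 evaluable pairs per arm, 60% carriage at day 6 in the control arm, and relative reductions of 25% (to 45%) and 20% (to 48%). From Blinding and Un-blinding: four tablets per dose. Assumed: two-sided alpha of 0.05, which the Protocol does not state but which fits its 95% intervals; and *f*, the share of the per-protocol azithromycin arm with visible tablet loss at 15 min or later. The documents give no value for *f*.

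**The plan's own figures.** 415 × 0.85 = 352.75, which rounds to 353. Normal-approximation power with pooled variance is Φ{[d − 1.96·√(2p̄(1−p̄)/n)] / √[(p₁(1−p₁)+p₂(1−p₂))/n]}.

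- 60% against 45%: (0.15 − 0.0737)/0.0372 = 2.05, so power is 98.0% (stated: 98%).
- 60% against 48%: (0.12 − 0.0735)/0.0372 = 1.25, so power is 89.4%. With a continuity correction it is 87.9%, and by exact Fisher enumeration 88.3% (stated: 88%).

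The planning figures reproduce, so they are a sound base for the dilution calculation.

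**Dilution model.** Let *L* be the fraction of benefit lost in an affected woman. The observed azithromycin prevalence is (1−f)·0.45 + f·(0.45 + L·0.15), and the ratio is that value divided by 0.60.

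- *L* = 0.25 (one of four tablets lost, benefit falling in proportion), *f* = 5%: 0.95 × 0.45 + 0.05 × 0.4875 = 0.4519; ratio 0.753.
- *L* = 1 (no benefit left), *f* = 5%: 0.95 × 0.45 + 0.05 × 0.60 = 0.4575; ratio 0.763.
- *f* = 10%: 0.4538, ratio 0.756 (*L* = 0.25); 0.465, ratio 0.775 (*L* = 1).

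On the *L* = 1 bound, the apparent relative reduction falls from 25% to 24.75% at *f* = 1%, 24.5% at 2%, 23.75% at 5% and 22.5% at 10%.

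**Scale against sampling error.** The standard error of the log ratio is √[0.55/(353 × 0.45) + 0.40/(353 × 0.60)] = 0.073, so the 95% interval around 0.750 is about 0.65 to 0.87. The shift to 0.763 is ln(0.7625/0.750) = 0.0165, about 0.23 standard errors. At *f* = 5% and *L* = 1, with 353 per arm, power is 96.8% if these women are retained and 97.5% if the same share is removed from both arms.

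**The case against.** The strongest objection concerns the remedy. Vomiting occurs after randomisation, and the Background lists gastrointestinal reactions to azithromycin. Widening the exclusion could remove more women from the active arm than from placebo, and applying the rule blind to arm does not prevent that. A short fixed window limits such exclusions. This stands as a cost. It is not decisive, because the 15-min rule already excludes on the same kind of event, and reporting exclusions by arm would show any imbalance.

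The effect is also small and of unknown frequency; the number of affected women could be zero. That stands too, and it limits the weight of the point. It does not remove the mismatch between what is recorded and what is used.

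A reader might go further and infer that women who took fewer than four tablets, or none, also count as fully dosed. The flow chart of "the number of mothers who were eligible, randomised and treated" might seem to support this. The Protocol does not bear it out. Those are ordinary flow-chart categories, the 15-min rule presupposes intake, no tablet count is described, and rules for untreated women commonly sit in a statistical analysis plan, which is not at hand. That inference rests on silence.

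A reader might also infer that agreement between the per-protocol and ITT results would be false reassurance in general. That is too strong: the per-protocol set still tests the effect of early vomiting, antibiotic use and late-arriving samples.

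**Conclusion.** The point holds in a limited form. The stated per-protocol rule ignores a recorded and more direct indicator of dose loss, so a woman with a tablet seen at 15 min or later is analysed as having received 2 g. Provided lost drug means lost benefit and affected women are otherwise like the rest of their arm, retaining them can only move the per-protocol estimate towards no effect. It cannot manufacture a benefit.

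With 60% control carriage and a true 25% reduction, an assumed 5% of the azithromycin arm affected moves the ratio from 0.750 to between 0.753 and 0.763. The upper figure is a worst case, and the 5% has no source in the documents. The ITT primary analysis, its test and the sample size are untouched.

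**What to change.** Reconcile the Randomization and Statistical analysis sections. Before unblinding and blind to arm, add one criterion to the existing per-protocol exclusions: mother/baby pairs in which an IMP tablet was recorded as seen in the vomitus. Report the number excluded by arm under each criterion. ITT stays primary.

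This takes one sentence and uses a field already collected. The Trial status section says data cleaning was ongoing, and the allocation code was to be held until after database lock, so the change could be made blind at that stage. The price is a slightly smaller set and the added selection risk described above, which the by-arm counts make visible.

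The change concerns the analysis set only. It says nothing about what sites do after a woman vomits.

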### Recruitment

Once eligibility was determined, baseline or pre-intervention samples were collected from the mother [nasopharyngeal swab (NPS) and vaginal swab].

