### Health centre discharge, follow up and sampling (Table 1 and Fig. 3)

Women were kept under close observation by study nurses. The JFPH nurses conducted the delivery. When the baby was born, the study nurse on duty collected the NPS within 6 h of birth. A clinical examination of both mother and baby were carried out by one of the study clinicians before discharge (Table 1), which occurred 6 to 24 h (mostly within 6–10 h) after delivery if both were clinically stable and there were no serious adverse events (SAE). Then, participants were given a Participant Identification (ID) card for further identification.

Home visits were conducted for each mother/baby pair for 8 weeks. In the first week, a nurse followed-up both mother and baby with daily recording of information on the health status of the pair and any adverse events (AE). During this week, samples were collected on days 3 and 6, including NPS from mother and baby and breast milk from the mother (Table 1).

Between the 8 and 10 days after the delivery, both mother and baby presented at the study site where the research clinician evaluated them and a vaginal swab was collected from the mother (Table 1). At that point, the babies presented at the infant welfare clinic to receive their BCG, OPVo, and Hepatitis B vaccines.

During the next 7 weeks, a field worker followed up the mother/baby pair. At weeks 2 and 4, breast milk samples were collected from the mothers and NPS from both mothers and babies (Table 1). If the baby was noted to have eye discharge during any of the visits, an eye swab was collected and clinical information recorded. Treatment was given appropriately.

In the advent of any symptoms or signs of illness during home visits, the field worker called the nurse coordinator who, if necessary, asked the mother and baby to go to the study site to be assessed by the nurse coordinator or his assistant or when indicated, by the study clinicians.

If during the follow-up period, either mother or baby needed antibiotics, samples were collected in lieu of the next scheduled sample and participants were started on antibiotics. If a mother was on antibiotics, no more samples were collected from her or the baby. If the baby was on antibiotics, subsequent samples were still collected from the mother.

**Table 1** Summary of the study activities including follow up visits and sampling

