## Discussion

Neonatal deaths, estimated at approximately 4 million annually, represent up to 40 % of all child fatalities with 3 out of 4 of these neonatal deaths occurring during the first week of life with maximum risk during the first 3–4 days. Interventions designed to impact on child mortality should target this vulnerable age group.

Sepsis causes up to 1 out of 3 neonatal deaths. Many neonatal casualties associated with sepsis are preventable when appropriate interventions are put into place. In resource-rich countries, GBS infections were substantially reduced with antibiotic-based prevention strategies. For example, chemoprophylaxis with ampicillin or penicillin in the USA reduced the incidence of early onset neonatal sepsis caused by GBS from 1.8 per 1,000 live births in the early 90's to 0.28 per 1,000 in 2010 [33]. In these countries, when a screened woman is identified as a GBS vaginal carrier, she is treated during labour intravenously with antibiotics [33, 34]. To reach maximum effectiveness, treatment should last at least 4 h before delivery [33, 34]. Maternal antibiotic treatment during labour blocks bacterial transmission to the newborn at birth. Because the newborn does not become infected, s/he is not at risk of developing early neonatal severe disease. Before GBS screening was introduced in USA and other developed countries, the great majority of neonatal sepsis, especially those occurring during the early neonatal period, were caused by this bacterium.

To roll-out a potentially successful intervention to developing countries within Africa and elsewhere, main epidemiological and contextual differences between the regions need to be considered. Unlike developed countries, several bacteria are associated with early and late neonatal sepsis in the African continent and intravenous antibiotics are generally unavailable. Approximately two thirds of neonatal sepsis cases in Africa are caused by gram positive bacteria [9] and in some countries gram positive bacteria represent up to 80 % of all sepsis during the first month as well as the first week of life. Due to costs, limited infrastructure and diagnostic facilities,

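### Newborn carriage acquisition is compared between arms among infants selected by carriage after treatment, so it is not a randomised comparison and can suggest a rebound on azithromycin that the drug did not cause

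*Protocol*

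**What the plan says.** Besides prevalence at each time point, the protocol's Statistical analysis section states that "carriage acquisition rates will be compared between arms for the periods 0–6 days and 7–28 days". It defines the event: "acquisition will happen when a non-carrier will become carrier in the subsequent sample". The at-risk group is therefore whoever was negative at the preceding swab. The estimate is also fixed: "Ratios of prevalence and 95 % confidence intervals will be calculated for each of these comparisons".

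On timing, the Recruitment section says that "baseline or pre-intervention samples were collected from the mother", and Table 1 shows no pre-intervention swab for the newborn. For the baby, "the study nurse on duty collected the NPS within 6 h of birth", which is after the dose in labour. Then "samples were collected on days 3 and 6, including NPS from mother and baby", with further newborn swabs at weeks 2 and 4.

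The protocol does not say whose acquisition is meant. Newborn nasopharyngeal carriage is the natural reading, though mothers may be included.

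**The concern.** Randomisation balances all newborns between arms. It does not balance newborns who are still negative at a swab taken after treatment, because the drug is meant to change who is negative. The Discussion says of the strategy on which the trial is modelled: "Maternal antibiotic treatment during labour blocks bacterial transmission to the newborn at birth".

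No newborn swab is scheduled between day 6 and week 2, so the 7–28 day at-risk group is naturally formed by the day-6 swab, the primary endpoint. If the drug works, some highly exposed newborns who would be carriers on placebo are negative on azithromycin. They enter the azithromycin at-risk group, while their placebo counterparts are left out. If high exposure also raises later acquisition, the azithromycin group starts with the worse mix.

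Such heterogeneity fits the trial's own premise that the mother is the main source of transmission, and its prevalence model adjusts for her baseline carriage. What is at stake is the interpretation: an apparent rebound, or the dilution of a real later benefit, could be read as a drug effect.

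**Working it through.** **The plan's own figures.** Sample size rationale: 415 pairs per arm, 15% loss, and carriage that "on day 6 was assumed to be 60 % in the control arm". 415 × 0.85 = 352.75, or 353 per arm. A 25% relative reduction means 60% to 45%; a 20% reduction means 60% to 48%. With two-sided alpha 0.05 (assumed), power is 98.0% and 89.4% (97.6% and 87.9% with continuity correction), against 98% and 88% stated. These agree and are not at issue.

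**Size of the day-6 at-risk groups (25% reduction).** Placebo: 1 − 0.60 = 0.40, and 353 × 0.40 = 141. Azithromycin: 1 − 0.45 = 0.55, and 353 × 0.55 = 194.

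**Model (all stratum figures are assumptions; the protocol gives none).** Half the newborns are high-exposure and half low-exposure, with placebo day-6 carriage pH and pL averaging 60%. Azithromycin multiplies both by 0.75 and has no effect after day 6. Days 7–28 are treated as one interval among day-6 non-carriers, with acquisition aH and aL the same in both arms.

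- High-exposure share of the at-risk group: s = 0.5(1 − pH) / [0.5(1 − pH) + 0.5(1 − pL)]. For azithromycin, use 0.75pH and 0.75pL.
- Acquisition: s·aH + (1 − s)·aL.

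Example, 80%/40%:

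- Placebo: 0.5 × 0.2 + 0.5 × 0.6 = 0.40; s = 0.10/0.40 = 25.0%.
- Azithromycin: 0.5 × 0.4 + 0.5 × 0.7 = 0.55; s = 0.20/0.55 = 36.4%.
- With later acquisition 80%/40%: 0.250 × 0.8 + 0.750 × 0.4 = 50.0%, against 0.364 × 0.8 + 0.636 × 0.4 = 54.5%. Ratio 1.09.

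| Day-6 placebo carriage, high/low | High-exposure share at risk, placebo / azithromycin | Later acquisition, high/low | Acquisition, placebo / azithromycin | Ratio |
|---|---|---|---|---|
| 60/60 | 50.0% / 50.0% | 60/20 | 40.0% / 40.0% | 1.00 |
| 70/50 | 37.5% / 43.2% | 70/50 | 57.5% / 58.6% | 1.02 |
| 70/50 | 37.5% / 43.2% | 40/20 | 27.5% / 28.6% | 1.04 |
| 70/50 | 37.5% / 43.2% | 60/20 | 35.0% / 37.3% | 1.06 |
| 80/40 | 25.0% / 36.4% | 80/40 | 50.0% / 54.5% | 1.09 |
| 80/40 | 25.0% / 36.4% | 40/20 | 25.0% / 27.3% | 1.09 |
| 80/40 | 25.0% / 36.4% | 60/20 | 30.0% / 34.5% | 1.15 |
| 90/30 | 12.5% / 29.5% | 40/20 | 22.5% / 25.9% | 1.15 |
| 90/30 | 12.5% / 29.5% | 80/30 | 36.3% / 44.8% | 1.24 |
| 90/30 | 12.5% / 29.5% | 60/20 | 25.0% / 31.8% | 1.27 |

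Within each stratum the true ratio is 1.00. If later acquisition does not differ by stratum (40/40), the ratio is 1.00 even with 90/30 early carriage, so exposure must predict both early and later carriage.

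**The denominator decides the direction.** In the last row, the proportion positive at day 6 or later among all newborns is 0.60 + 0.40 × 0.250 = 70.0% on placebo and 0.45 + 0.55 × 0.318 = 62.5% on azithromycin. The randomised comparison favours azithromycin while the conditional one points the other way.

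**Masking.** In the 90/30 row with later acquisition 80/30, a true 20% later reduction in both strata would appear as 0.80 × 1.235 = 0.99.

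**The case against.** The strongest reply is that little depends on this analysis. It is additional, and acquisition is neither the primary nor a listed secondary endpoint. Prevalence is compared by arm at every time point without conditioning on earlier carriage, and a Poisson model covers all time points. A spurious rebound would therefore appear beside day-14 and day-28 prevalence. This stands, and it limits the harm.

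The size is also assumed and mostly modest. For 50.0% against 54.5% with 141 and 194 at risk, the standard error of the log ratio is √(0.5/70.5 + 0.455/105.8) = 0.107, giving a 95% interval of about 0.89 to 1.34. The bias in that case lies well within sampling error. This stands too, but a bias that follows from the design is not excused by low precision.

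Three stronger readings are tempting, and the protocol does not support them.

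- **That Fisher's test is misapplied to a rate.** The protocol ties that test to prevalence comparisons; only the ratios and intervals clearly extend to acquisition. Nor does a child supply several events per period. With three yes/no swabs (days 0, 3, 6 or days 6, 14, 28), at most one negative-to-positive change can occur, so acquired or not is already one outcome per child.
- **That the mothers' analysis needs the same repair.** Their first nasopharyngeal interval starts from a pre-dose swab and is sound. Fixing their risk status at that swab for both periods would count a mother first positive on day 3 or 6, and still positive on day 14, as a day 7–28 acquisition, contrary to the protocol's definition.
- **That an excess on azithromycin is certain, or that the main result is compromised.** It needs heterogeneity that the protocol does not quantify, and the primary analysis does not condition on carriage.

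**Conclusion.** The point holds for newborns. The planned acquisition comparison conditions on carriage measured after treatment, and its two at-risk groups (about 40% and 55% of newborns at the design assumptions) are not randomised groups. With no drug effect after day 6 and a 25% early reduction, the azithromycin:placebo ratio is 1.00 if newborns are homogeneous, about 1.02 to 1.15 with mild to moderate heterogeneity, and up to about 1.27 with strong heterogeneity. These figures rest on the assumed strata and show what is possible, not what will happen.

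The problem is clearest for days 7–28. The days 0–6 comparison is also conditional, but its bias depends on how far the drug has already changed the birth and day-3 swabs, and no size is given here. The primary intention-to-treat comparison, its power and the prevalence comparisons at each time point are unaffected. The change is worth making because it is cheap and prevents a misreading.

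**What to change.** In the Statistical analysis section:

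1. Make the between-arm newborn comparison on all sampled randomised newborns: the proportion with any carriage by day 6, and the proportion with any carriage at days 14–28. Read these beside the planned day-14 and day-28 prevalence.
2. Report swab-to-swab newborn acquisition descriptively by arm, labelled as conditional on post-randomisation carriage and not as a treatment effect.
3. State whether acquisition refers to newborns, mothers or both. Leave the mothers' first nasopharyngeal interval as it is.

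Adjusting acquisition for maternal baseline carriage would reduce the selection but not remove it, so it does not replace the first step.

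The cost is a change of wording and analysis on the same swabs; the Trial status section says laboratory work and data cleaning were still under way. The downside is that acquisition among newborn non-carriers is no longer an inferential comparison.

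### The day-6 primary analysis could use pre-dose maternal carriage at almost no cost: Fisher's unadjusted test is valid, and the gain from adjusting is real only if maternal carriage is prognostic

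*Protocol*

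**What the plan says.** The Statistical analysis section of the protocol compares carriage between arms at each sampling time. It reports a prevalence ratio with a 95 % confidence interval, and Fisher's "exact test will be used to compute p-values for the comparisons of prevalence". The primary endpoint, newborn nasopharyngeal carriage of any of the three bacteria at day 6, falls under this rule. No covariate enters, and no method is named for the interval.

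Under Recruitment, "baseline or pre-intervention samples were collected from the mother"; these are a nasopharyngeal and a vaginal swab. In the Statistical analysis section they serve two purposes. They are part of the check that the arms are comparable at baseline, and maternal baseline carriage is a covariate in one model: "A Poisson regression model will be used to assess the effect of the intervention on prevalence of carriage across all time points". That model uses robust standard errors. The two extra analyses named for the primary outcome are a subgroup of women who delivered at least 2 h after dosing and a multiple-imputation analysis. Neither is described as covariate-adjusted.

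The Sample size rationale gives "353 participants in each arm for whom the primary endpoint is recorded", carriage that "on day 6 was assumed to be 60 % in the control arm", and "88 % power to detect a 20 % reduction".

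**The concern.** The Discussion rests the trial on the idea that infants acquire these bacteria chiefly from their mothers. If so, maternal carriage before dosing should predict infant carriage at day 6, and adjusting for it would narrow the primary interval and absorb chance imbalance between arms. The data are collected and a suitable model is already planned, but the protocol does not state that model for day 6. If the comparability check showed an imbalance in maternal carriage, no stated day-6 analysis would deal with it.

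Separately, a Fisher p-value printed beside a ratio interval from another method can give two different answers to the same question. At stake are some precision and the coherence of the primary result, not its validity.

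**Working it through.** **Inputs.** From the protocol: 415 per arm; the plan "assumed a 15 % loss to follow-up", and 415 × 0.85 = 352.75, so n = 353; control carriage 60 %; relative reductions of 25 % (to 45 %) and 20 % (to 48 %). Assumed, because the protocol does not give them: two-sided 0.05 (inferred from the 95 % level); a log-scale Wald interval for the ratio; maternal carriage in 50 % of women; infant carriage by maternal status as shown below.

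**1. The plan's power.** Power = Φ{[d − 1.96√(2p̄(1−p̄)/n)] / √[(p₁(1−p₁)+p₂(1−p₂))/n]}.
- 60 vs 48 %: (0.12 − 0.0735)/0.0372 = 1.248, power 89.4 %.
- 60 vs 45 %: (0.15 − 0.0737)/0.0372 = 2.054, power 98.0 %.

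Exact enumeration of Fisher's test gives 88.3 % and 97.6 %. The stated 88 % and 98 % are reproduced, and 88 % fits the test that the plan names.

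**2. Fisher against chi-square (exact enumeration, 353 per arm).** Size at 60 vs 60 %: Fisher 4.2 %, chi-square 5.0 %. Power at 60 vs 48 %: 88.3 % and 89.6 %, a difference of 1.3 points.

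**3. Disagreement between p-value and interval.** Example: 212/353 vs 186/353. Ratio = 186/212 = 0.877, log ratio −0.1308, SE = √(1/212 − 1/353 + 1/186 − 1/353) = 0.06654. The interval is exp(−0.1308 ± 1.96 × 0.06654) = 0.770 to 0.9996, with Fisher p = 0.058. Over all possible tables, the probability of disagreement is 0.2 % at 60/45, 0.7 % at 60/48, 1.3 % at 60/50, 2.4 % at 60/54 and 0.8 % at 60/60. For practical purposes it always runs one way: the interval excludes 1 while Fisher is not significant.

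**4. Gain from adjustment at 60 vs 48 %.** For the log prevalence ratio, n × variance is Σ(1−p)/p over arms when unadjusted: 0.40/0.60 + 0.52/0.48 = 1.750. For the robust Poisson model with arm and maternal carriage, it is Σ[w + f]/p² over arms. Here w is the average within-stratum p(1−p), and f is the average squared difference between true and fitted stratum prevalence. Effective-sample gain = 1.750 / adjusted value − 1.

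| Control carriage, carrier / non-carrier mothers | Treated carriage | w control, w treated | f per arm | n × variance | Gain |
|---|---|---|---|---|---|
| 60 / 60 (not prognostic) | 48 / 48 | 0.2400, 0.2496 | 0 | 1.750 | 0 % |
| 70 / 50, constant ratio | 56 / 40 | 0.2300, 0.2432 | 0 | 1.694 | 3 % |
| 75 / 45, constant ratio | 60 / 36 | 0.2175, 0.2352 | 0 | 1.625 | 8 % |
| 80 / 40, constant ratio | 64 / 32 | 0.2000, 0.2240 | 0 | 1.528 | 15 % |
| 70 / 50, benefit in carriers only | 46 / 50 | 0.2300, 0.2492 | 0.0031 | 1.742 | 0.4 % |
| 75 / 45, benefit in carriers only | 51 / 45 | 0.2175, 0.2487 | 0.0025 | 1.701 | 3 % |
| 80 / 40, benefit in carriers only | 56 / 40 | 0.2000, 0.2432 | 0.0020 | 1.625 | 8 % |

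The fitted ratio is 0.48/0.60 = 0.80 in every row, so adjustment does not change what is estimated.

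**5. In power terms.** Power = Φ(0.2231/√(V/353) − 1.96), where 0.2231 = −ln 0.80 and V is the n × variance column. The unadjusted ratio test gives 88.7 %. With a constant ratio, adjustment gives 89.6 %, 90.8 % and 92.4 %. In a simulation of 3,000 replicates with a constant ratio, chi-square gave 89.7, 90.0 and 89.5 % and adjusted Poisson 89.9, 92.1 and 93.1 %. In a separate simulation of 1,500 replicates, the adjusted test had null size 0.047.

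**The case against.** The strongest reply is that nothing needs correcting. Fisher's test controls the type I error, the trial is sized for it, and an unadjusted ratio under intention to treat is a transparent primary result. All of that stands.

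Part of any power gain over Fisher comes only from leaving Fisher. At 70/50 the adjusted model has about the same power as an unadjusted chi-square test (89.6 % for both), so adjustment itself buys something only when the association is stronger. That stands too.

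The trial's mechanism also cuts both ways. If treatment works by blocking transmission from carrier mothers, it weakens the link between pre-dose maternal carriage and infant carriage in the treated arm. The lower rows of the table show the gain shrinking, almost to nothing at 70/50.

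The disagreement between p-value and interval is rare, confined to borderline results, and depends on an interval method the protocol does not name. The across-time model includes maternal carriage, and a statistical analysis plan that was not available here may draw day-specific effects from it. Finally, recruitment had finished when the protocol was published, so replacing a stated primary test needs justification even while blinded.

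These points limit the size of the claim. They do not remove the case for using a baseline measure already in hand, because adjusting costs essentially nothing even if it proves uninformative.

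**Conclusion.** This is a low-cost improvement, not an error. The protocol leaves the day-6 comparison unadjusted although a plausible prognostic baseline is measured before dosing and a suitable model is already planned.

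The exact results, at 353 per arm and two-sided 0.05, are a Fisher size of 4.2 % and 1.3 points less power than chi-square at 60 vs 48 %. The 0.2 to 2.4 % disagreement also assumes a log-scale Wald interval. The precision gain is conditional on an association the protocol does not report: none, about 3 to 15 %, or about 0.4 to 8 %, according to the scenario.

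A reader might infer that precision is certainly being thrown away, that the primary result will contradict itself, or that no adjusted day-6 estimate can ever appear. The protocol supports none of these. It gives no infant carriage by maternal status, disagreement would be uncommon, and reporting by time point from the planned model may be settled elsewhere.

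**What to change.** Before unblinding, state that the primary result is the day-6 prevalence ratio from the robust Poisson model already planned, fitted to day-6 data and adjusted for pre-dose maternal nasopharyngeal and vaginal carriage. Take the ratio, 95 % confidence interval and p-value from that one model. Cluster the standard errors on the mother, which also covers the few twins. Say how a missing baseline swab is handled, so that no infant leaves the intention-to-treat analysis because of it. Report the crude ratio with Fisher's test as supportive.

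The cost is wording in the analysis plan; no new data are needed. The protocol describes laboratory work and data cleaning as ongoing and allows the code to be broken only after database lock, so the change could be made blind. The small downside is that it alters the stated primary test, so the date, the reason and the blinded status should be recorded.
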